## 12.3 Compensation

The patients/patients’ families will receive reimbursement for transportation costs to and from the clinic. In addition, all clinic visits, antimalarial medication, and the evaluation and treatment for some routine medical problems encountered during follow-up will be provided free of charge. Medical care that the patient receives which is unrelated to malaria will remain the primary responsibility of the patient, parent or guardian, although routine medical problems will generally be managed by the study at no cost to the patient.

## 12.4 Consent procedures

All screening interviews will be conducted in the native language of the patients by the study personnel (with a translator if necessary). Consent forms will be provided to the patients / parents or guardians for their review. The study clinicians at the clinic will seek formal consent. The patients / parents or guardians will be asked to sign consent to participate in a research study. The informed consent will describe the purpose of the study, the procedures to be followed, and the risks and benefits of participation. If a patient, parent or guardian is unable to read or write, his/her fingerprint will be used in substitute for a signature, and a signature from a witness to the informed consent discussion will be obtained. Patients / parents or guardians will be informed that participation in the study is completely voluntary and that they may withdraw from the study at any time.

## 12.5 Alternatives

Individuals whose parents or guardians choose not to participate in this study will not be enrolled. They will receive standard care for medical problems as they arise at the government health dispensaries or other medical facilities in the UMSP sentinel sites.

## 12.6 Confidentiality of records

Patients, parents and guardians will be informed that participation in a research study may involve a loss of privacy. All records will be kept as confidential as possible. Patients will be identified primarily by their study number and patient names will not be entered into the computerized database. No individual identities will be used in any reports or publications resulting from the study.

# 13.0 TIMETABLE

**Table 6. Timetable for Study Activities**

|  | **2004** | | | | | | | | | | | |
| --- | --- | --- | --- | --- | --- | --- | --- | --- | --- | --- | --- | --- |
| **J** | **F** | **M** | **A** | **M** | **J** | **J** | **A** | **S** | **O** | **N** | **D** |
| **Finalization/approval of study protocol** |  |  |  |  |  | X | X |  |  |  |  |  |
| **Database design** |  |  |  |  |  |  | X |  |  |  |  |  |
| **Personnel training** |  |  |  |  |  |  | X |  |  |  |  |  |
| **Pilot study** |  |  |  |  |  |  | X |  |  |  |  |  |
| **Recruitment** |  |  |  |  |  |  | X | X | X | X | X |  |
| **Follow-up** |  |  |  |  |  |  | X | X | X | X | X |  |
| **Data entry/analysis** |  |  |  |  |  |  | X | X | X | X | X |  |
| **Manuscript preparation** |  |  |  |  |  |  |  |  |  |  | X | X |

# APPENDIX 1. PARTICIPANT SELECTION AND ENROLLMENT

Patients attending OPD aged 1 – 10 years with history of recent fever

Send to laboratory

Screening thick blood smear

Negative smear or parasitaemia > 2000 < 200,000 parasites/ul

< 2,000 or > 200,000 /ul

Refer patient to clinician

Refer patient back to OPD

No information collected

Complete Screening Form

Excluded Passed Initial Screening

Complete Informed Consent Form

Excluded

Refer patient back to OPD

Save screening form only

Assign Study Number

#### Excluded

Complete Case Record Forms

Excluded

Refer to the Laboratory

Hb < 5.0

Schedule Follow up Visits

Refer to the Study Nurse

Assign Treatment Number

Thin and thick smear read overnight

Meet additional inclusion criteria on Day 1?

*P. falciparum* monoinfection

Parasite density > 2000 <200000/ul

**Yes**

**No**

**Excluded on Day 1**

**(Treat as appropriate)**

**Continue with scheduled follow-up outlined in appendix 4.**

# Appendix 2: Patient Screening Form

**STUDY SITE CODE:________ STUDY NUMBER: ___________________________**

UMSP SCREENING FORM

| **1. Names:** | **2. Date: *(dd/mm/yy)*** | **3.Weight (kg):** |
| --- | --- | --- |
| **4. Age*: _______years __________months.** | **5. Gender: M _______ F_______** | |

****Include months only if age < 5 years, if age is above 5 years write*** “X”

| **SCREENING selection criteria**  ***Patients who are 1-10 years of age and have a positive screening thick blood smear.*** | | |
| --- | --- | --- |
| **inclusion criteria** | **yes** | **NO** |
| 6. Fever (> 37.5C) or history of fever in previous 24 hours |  |  |
| 7. Weight > 10 kg |  |  |
| 8. Ability to participate in 28 day follow up. |  |  |
| **EXCLUSION CRITERIA** | **NO** | **YES** |
| 9. Previously participated in this study? |  |  |
| 10. History of serious side effects to study medications  *If present, indicate drug / side effect:*   Amodiaquine:________________________   Artesunate:__________________________   Coartemether:________________________ |  |  |
| 11. Evidence of severe malaria / danger signs  *If “ YES” indicate criteria. If “NO”, leave blank.*  Unarousable coma *(if after convulsion, > 30 min)*   Repeated convulsions *(> 2 within 24 h)*   Recent convulsions *(1-2 within 24 h)*   Altered consciousness *(confusion, delirium, coma)*   Lethargy   Unable to drink or breast feed   Vomiting everything   Unable to stand/sit due to weakness   Severe anaemia *(Hb < 5.0 g/dL)*   Respiratory distress *(laboured breathing at rest)*   Jaundice *(yellow coloring of eyes)* |  |  |
| 12. Evidence of concomitant febrile illness  *If “YES”, indicate illness. If “NO”, leave blank.*   Pneumonia/RTI  Measles   Otitis Media  UTI   Gastroenteritis  Other:_________________ |  |  |
| **INCLUSION CRITERIA** | **YES** | **NO** |
| 13. Provision of informed consent. |  |  |
| 14. Absence of persistent vomiting of study medications on day 0 |  |  |
| ***Complete prior to day 1 clinic visit.*** | | |
| 15. *P. falciparum* mono-infection |  |  |
| 16. Parasite density > 2000/ul and < 200,000/ul  *If “NO” specify density* < 2000/ul  > 200,000/ul |  |  |

***If any of the responses fall into the shaded area, exclude the patient from the study***

# APPENDIX 3. UMSP ENROLLMENT FORM.

| **enrollment form** | | |
| --- | --- | --- |
| **1. Study**  **Number:** | **2. Treatment**  **Number:** | **3. Start Date:**  ***(dd/mm/yy)*** |

| 4. Patients name: |
| --- |
| 5. Father’s/Husband’s (if married) name: |
| 6. Mother’s/Wife’s (if married) name: |
| 7. Primary caregiver / guardian’s name and relationship (N/A if mother or father): |
| 8. Sub county of residence. |
| 9. Home parish: |
| 10. LC1/village: |
| 11. Home address and localising features: |
| 12. a) Phone number: Yes ___No ___  If yes: b) Phone number (s) and the owner(s): |
| Patient Information |
| 13. Does the patient use malaria preventive measures: Yes ___No ___Unknown ____  If yes, which measures are used?    a) Spray: Yes ___No ___  b) Coils: Yes ___No ___  c) Chemoprophylaxis: Yes ___No ___  If yes, which drug? ___________________________________  d) Bed net: Yes ___No ____  If yes, is the net treated? Yes ___No ___   How often does the patient sleep under the net?  Always____ Often \ Sometimes____  e) Other protective measures ______________________________________________________________ |

# APPENDIX 4. Critical steps

**Day 1.**

Evaluate patient and complete Case Record Form. Administer study medications (DOT).

**Day 2.**

Evaluate patient and complete Case Record Form. Administer study medications (DOT)

Collect thick blood smear and filter paper sample

**Day 3.**

Evaluate patient and complete Case Record Form. Collect thick blood smear and filter paper sample

**Day 7, 14, 21**. Evaluate patient and complete Case Record Form. Collect thick blood smear and filter paper sample

**Any Unscheduled Day (Day 4-27).**

Evaluate patient and complete Case Record Form. Collect thick blood smear with filter paper sample.

D2 Parasitaemia > D 0 parasitaemia

**ETF**

**Treat with oral quinine**

**Severe disease or danger signs**

Do urgent thick smear, FP sample and Haemoglobin

If patient has

1. Temperature > 37.50C with parasitaemia

2. Parasite count >25% Day 0 count.

**ETF**

**Treat with oral quinine**

**Day 28.**

Evaluate patient and complete Case Record Form. Collect thick blood smear and filter paper sample.

**Severe disease or danger signs**

Do urgent thick smear, FP sample and Haemoglobin

Negative smear

**Continue study**

**Rx at your discretion.**

Negative smear

**Continue study Rx at your discretion.**

Positive blood smear

**ETF**

**Give/ refer for IV quinine Rx.**

Positive blood smear

**LCF**

**Give/ refer for IV Quinine Rx.**

**ACPR** No parasitaemia on day 28 irrespective of fever history or temperature.

**LPF** Parasitaemia D 28 with temperature < 37.50C without being ETF or LCF.

# Day 2 > Day 0

## ETF

Rx with quinine

Refer for care?

# Day 2 < Day 0

Assess for DDx

Cont. study Rx

Refer for care?

# Yes

## ETF

Rx with quinine

'

If patient has

1. Temp > 37.5C with parasitaemia

2. History of fever in the last 24 hours with parasitaemia.

**Do Haemoglobin and thin blood smear**

LCF

Treat with oral quinine

Patients who are LPF’s should be treated with oral quinine.

# Appendix 6a. Weight-based administration of study medications for AQ+AS group

| **Weight (kg)** | **Amodiaquine (AQ)**  **200 mg tabs (Base)** | | | **Artesunate (AS)**  **50 mg tabs** | | | **Placebo tablets** | | |
| --- | --- | --- | --- | --- | --- | --- | --- | --- | --- |
|  | **Day 0** | **Day 1** | **Day 2** | **Day 0** | **Day 1** | **Day 2** | **Day 0** | **Day 1** | **Day2** |
|  | **am** | **am** | **am** | **am** | **am** | **am** | **pm** | **pm** | **pm** |
| 10 | ½ | ½ | ¼ | ¾ | ¾ | ¾ | 1 | 1 | 1 |
| 11 | ½ | ½ | ¼ | 1 | 1 | 1 | 1 | 1 | 1 |
| 12 | ½ | ½ | ½ | 1 | 1 | 1 | 1 | 1 | 1 |
| 13 | ½ | ½ | ½ | 1 | 1 | 1 | 1 | 1 | 1 |
| 14 | ¾ | ½ | ½ | 1 ¼ | 1 ¼ | 1 ¼ | 1 | 1 | 1 |
| 15 | ¾ | ½ | ½ | 1 ¼ | 1 ¼ | 1 ¼ | 2 | 2 | 2 |
| 16 | ¾ | ¾ | ½ | 1 ¼ | 1 ¼ | 1 ¼ | 2 | 2 | 2 |
| 17 | ¾ | ¾ | ½ | 1 ½ | 1 ½ | 1 ½ | 2 | 2 | 2 |
| 18 | 1 | ¾ | ½ | 1 ½ | 1 ½ | 1 ½ | 2 | 2 | 2 |
| 19 | 1 | ¾ | ½ | 1 ½ | 1 ½ | 1 ½ | 2 | 2 | 2 |
| 20 | 1 | 1 | ½ | 1 ¾ | 1 ¾ | 1 ¾ | 2 | 2 | 2 |
| 21 | 1 | 1 | ½ | 1 ¾ | 1 ¾ | 1 ¾ | 2 | 2 | 2 |
| 22 | 1 ¼ | 1 | ½ | 1 ¾ | 1 ¾ | 1 ¾ | 2 | 2 | 2 |
| 23 | 1 ¼ | 1 | ½ | 2 | 2 | 2 | 2 | 2 | 2 |
| 24 | 1 ¼ | 1 ¼ | ½ | 2 | 2 | 2 | 2 | 2 | 2 |
| 25 | 1 ¼ | 1 ¼ | ½ | 2 | 2 | 2 | 3 | 3 | 3 |
| 26-27 | 1 ¼ | 1 | 1 | 2 ¼ | 2 ¼ | 2 ¼ | 3 | 3 | 3 |
| 28 | 1 ¼ | 1 ¼ | 1 | 2 ¼ | 2 ¼ | 2 ¼ | 3 | 3 | 3 |
| 29-31 | 1 ¼ | 1 ¼ | 1 | 2 ½ | 2 ½ | 2 ½ | 3 | 3 | 3 |
| 32 | 1 ½ | 1 ½ | 1 | 2 ½ | 2 ½ | 2 ½ | 3 | 3 | 3 |
| 33 | 1 ½ | 1 ½ | 1 | 2 ¾ | 2 ¾ | 2 ¾ | 3 | 3 | 3 |
| 34 | 1 ½ | 1 ½ | 1 ¼ | 2 ¾ | 2 ¾ | 2 ¾ | 3 | 3 | 3 |
| 35 | 1 ½ | 1 ½ | 1 ¼ | 2 ¾ | 2 ¾ | 2 ¾ | 4 | 4 | 4 |
| 36-37 | 1 ½ | 1 ½ | 1 ¼ | 3 | 3 | 3 | 4 | 4 | 4 |
| 38 | 2 | 1 ½ | 1 ¼ | 3 | 3 | 3 | 4 | 4 | 4 |
| 39 | 2 | 1 ½ | 1 ¼ | 3 ¼ | 3 ¼ | 3 ¼ | 4 | 4 | 4 |
| 40-43 | 2 | 2 | 1 | 3 ¼ | 3 ¼ | 3 ¼ | 4 | 4 | 4 |
| 44-47 | 2 | 2 | 1 ½ | 3 ½ | 3 ½ | 3 ½ | 4 | 4 | 4 |
| 48-49 | 2 | 2 | 2 | 3 ¾ | 3 ¾ | 3 ¾ | 4 | 4 | 4 |
| 50-59 | 2 ½ | 2 | 2 | 4 | 4 | 4 | 4 | 4 | 4 |
| >60 | 3 | 3 | 1 ½ | 5 | 5 | 5 | 4 | 4 | 4 |

# Appendix 6b. Weight-based administration of study medications for coartemether group

| **Weight (kg)** | **Placebo tablets** | | | **Coartemether**  **20mg /120 mg tabs** | | | | | |
| --- | --- | --- | --- | --- | --- | --- | --- | --- | --- |
|  | **Day 0** | **Day 1** | **Day 2** | **Day 0** | | **Day 1** | | **Day 2** | |
|  | am | am | am | am | pm | am | pm | am | pm |
| 10 | ½ | ½ | ¼ | 1 | 1 | 1 | 1 | 1 | 1 |
| 11 | ½ | ½ | ¼ | 1 | 1 | 1 | 1 | 1 | 1 |
| 12 | ½ | ½ | ½ | 1 | 1 | 1 | 1 | 1 | 1 |
| 13 | ½ | ½ | ½ | 1 | 1 | 1 | 1 | 1 | 1 |
| 14 | ¾ | ½ | ½ | 1 | 1 | 1 | 1 | 1 | 1 |
| 15 | ¾ | ½ | ½ | 2 | 2 | 2 | 2 | 2 | 2 |
| 16 | ¾ | ¾ | ½ | 2 | 2 | 2 | 2 | 2 | 2 |
| 17 | ¾ | ¾ | ½ | 2 | 2 | 2 | 2 | 2 | 2 |
| 18 | 1 | ¾ | ½ | 2 | 2 | 2 | 2 | 2 | 2 |
| 19 | 1 | ¾ | ½ | 2 | 2 | 2 | 2 | 2 | 2 |
| 20 | 1 | 1 | ½ | 2 | 2 | 2 | 2 | 2 | 2 |
| 21 | 1 | 1 | ½ | 2 | 2 | 2 | 2 | 2 | 2 |
| 22 | 1 ¼ | 1 | ½ | 2 | 2 | 2 | 2 | 2 | 2 |
| 23 | 1 ¼ | 1 | ½ | 2 | 2 | 2 | 2 | 2 | 2 |
| 24 | 1 ¼ | 1 ¼ | ½ | 2 | 2 | 2 | 2 | 2 | 2 |
| 25 | 1 ¼ | 1 ¼ | ½ | 3 | 3 | 3 | 3 | 3 | 3 |
| 26-27 | 1 ¼ | 1 | 1 | 3 | 3 | 3 | 3 | 3 | 3 |
| 28 | 1 ¼ | 1 ¼ | 1 | 3 | 3 | 3 | 3 | 3 | 3 |
| 29-31 | 1 ¼ | 1 ¼ | 1 | 3 | 3 | 3 | 3 | 3 | 3 |
| 32 | 1 ½ | 1 ½ | 1 | 3 | 3 | 3 | 3 | 3 | 3 |
| 33 | 1 ½ | 1 ½ | 1 | 3 | 3 | 3 | 3 | 3 | 3 |
| 34 | 1 ½ | 1 ½ | 1 ¼ | 3 | 3 | 3 | 3 | 3 | 3 |
| 35 | 1 ½ | 1 ½ | 1 ¼ | 4 | 4 | 4 | 4 | 4 | 4 |
| 36-37 | 1 ½ | 1 ½ | 1 ¼ | 4 | 4 | 4 | 4 | 4 | 4 |
| 38 | 2 | 1 ½ | 1 ¼ | 4 | 4 | 4 | 4 | 4 | 4 |
| 39 | 2 | 1 ½ | 1 ¼ | 4 | 4 | 4 | 4 | 4 | 4 |
| 40-43 | 2 | 2 | 1 | 4 | 4 | 4 | 4 | 4 | 4 |
| 44-47 | 2 | 2 | 1 ½ | 4 | 4 | 4 | 4 | 4 | 4 |
| 48-49 | 2 | 2 | 2 | 4 | 4 | 4 | 4 | 4 | 4 |
| 50-59 | 2 ½ | 2 | 2 | 4 | 4 | 4 | 4 | 4 | 4 |
| >60 | 3 | 3 | 1 ½ | 4 | 4 | 4 | 4 | 4 | 4 |

# APPENDIX 7. CLASSIFICATION OF RESPONSE TO TREATMENT

**Early Treatment Failure (ETF)**

| **ETF**   - Development of danger signs or severe malaria on Day 1, Day 2 or Day 3 in the presence of parasitemia - Parasitaemia on day 2 higher than Day 0 count irrespective of axillary temperature. - Parasitaemia on Day 3 with axillary temperature > 37.5 0C - Parasitaemia on Day 3 > 25% of count on Day 0. - Severe AE requiring change in treatment Days 0 - 2 |
| --- |

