## 4.2 Study outcome and assessment

### 4.2.1 Classification of treatment outcome

Response to treatment will be classified according the recently proposed WHO classification system, and will include adequate clinical and parasitological response (ACPR), early treatment failure (ETF), late clinical failure (LCF), and late parasitological failure (LPF), for purposes of data reporting (Appendix 3). [26] In the final analysis, treatment outcomes will be dichotomized based on the following definitions:

- Clinical rescue therapy = ETF + LCF
- Parasitological rescue therapy = ETF + LCF + LPF.

All ETFs will be considered true treatment failures. For all LCFs and LPFs, molecular genotyping will be used to distinguish recrudescence (true treatment failure) from new infection (see section 11.3).

- Clinical treatment failure = All ETFs + LCFs due to recrudescence
- Parasitological treatment failure = All ETFs + LCFs/LPFs due to recrudescence

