**Late Treatment Failure (LTF)**

| **Late Clinical Failure (LCF):**   - Development of danger signs or severe malaria after Day 3 in the presence of parasitemia, without previously meeting any of the criteria of early treatment failure - Presence of parasitaemia and axillary temperature > 37.5C, (or history of fever in past 24 hours), on any day from Day 4 to Day 28, without previously meeting any of the criteria of early treatment failure   **Late Parasitological Failure (LPF):**   - Presence of parasitemia on Day 28 and axillary temperature < 37.5C, without previously meeting any of the criteria of early treatment failure or late clinical failure |
| --- |

Adequate Clinical and Parasitological Response (ACPR)

| **ACPR**   - Absence of parasitemia on Day 28 irrespective of temperature without previously meeting any of the criteria of early treatment failure or late clinical failure or late parasitological failure. |
| --- |

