****(Grade on scale of 0-4: normal = 0; mild abnormality = 1; moderate = 2; severe = 3, life-threatening = 4)***

***† Any haemoglobin <*** 5g/dl measured after Day 0 is a serious AE. Notify Kampala core facility immediately of all serious adverse events.

| **RECORD OF ADDITIONAL MEDICATION GIVEN DURING STUDY** | | | | |
| --- | --- | --- | --- | --- |
| **Medication (a)** | **Indication (b)** | **Dose (c)** | **Duration (d)** | **Date started (e)** |
| **60.** |  |  |  |  |
| **61.** |  |  |  |  |
| **62.** |  |  |  |  |
| **63.** |  |  |  |  |
| **64.** |  |  |  |  |
| **65.** |  |  |  |  |
| 66. |  |  |  |  |
| **67.** |  |  |  |  |
| **68.** |  |  |  |  |
| **69.** |  |  |  |  |
| **70.** |  |  |  |  |

| **UMSP clinical record form (4):** | | | |
| --- | --- | --- | --- |
| **Patient**  **Initials:** | **1. Study Number: U**|___|___|___|___|___| | **2. Day 0 Date:** |___|___|/|___|___|/|___|___|  ***day month year*** | **3. Treatment Number:** |___|___|___| |

| complete efficacy outcome | |
| --- | --- |
|  ETF     LCF   LPF   ACPR     N/A (Tick appropriate Incomplete Efficacy Outcome **)** | If failed, **STUDY DAY** of clinical failure (0-28) __________  **Reason for ClinicalFailure:**   Severe malaria/danger signs with parasitemia Days 0-3  Specify criteria _________   Severe AE requiring change in treatment Days 0-2  Specify criteria _____________   Day 2 parasite count > Day 0 count   Parasitemia on Day 3 with temperature > 37. 5   Day 3 parasite count > 25% Day 0 count   Severe malaria with parasitemia Days 4-28  Specify criteria __________________   Parasitemia on Days 4-28 with temperature > 37. 5 OR History of fever in past 24 hours. |

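### The outcome form and Appendix 7 define danger-sign failures differently, on Day 0 and again after Day 3, so a small group may be coded inconsistently on the primary endpoint

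*Protocol*

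**What the plan says.** Section 4.2.1 defines the endpoint as "Clinical rescue therapy = ETF + LCF", and section 4.2.2 makes its risk the primary outcome. The same section treats every ETF as a true treatment failure; only late failures are genotyped.

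Appendix 7 gives the criteria. For ETF, the danger-sign criterion is "Development of danger signs or severe malaria on Day 1, Day 2 or Day 3 in the presence of parasitemia", and a separate criterion reads "Severe AE requiring change in treatment Days 0 - 2". For LCF, it has "Development of danger signs or severe malaria after Day 3 in the presence of parasitemia", plus a route through fever or reported fever from Day 4 to Day 28.

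The outcome form (Appendix 12, clinical record form 4) lists reasons for failure. The early one is "Severe malaria/danger signs with parasitemia Days 0-3", and the key beneath the form also has ETF assessed from Day 0. The late ones are "Severe malaria with parasitemia Days 4-28" and "Parasitemia on Days 4-28 with temperature > 37. 5 OR History of fever in past 24 hours". Appendix 8 keeps severe malaria and danger signs as two separate lists.

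The documents do not settle which text governs. Sections 4.1 and 7.2 point to Appendix 7. Section 4.2.1 points to Appendix 3, which here is the enrolment form. The outcome form sends staff to a clinic poster, a field manual and an SOP for the exact definitions.

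**The concern.** Site staff record the primary endpoint on the form, while the protocol text defines it through Appendix 7. The two differ at the start of the early window and in the content of the late one. The late omission does not read as shorthand, because the early line of the same form names danger signs explicitly.

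Both components of the primary outcome are affected. Section 9.2 restricts the efficacy analysis to patients who have an outcome, so a coding difference can change the denominator as well as the number of failures. With four sites and several cited sources for the definitions, nothing in the protocol ensures that the same child is coded the same way everywhere.

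**Working it through.** **1. The plan's own figure (background only).** Section 9.1 has 200 per arm per site, 10% loss, two-sided α = 0.05, 80% power, an AQ+AS risk of 40–50% and a detectable difference of about 15%. Evaluable per arm: 200 × 0.90 = 180. The formula is n = [1.96·√(2·p̄·(1−p̄)) + 0.842·√(p1(1−p1) + p2(1−p2))]² / (p1−p2)².

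For 45% against 30%: [1.96·√0.46875 + 0.842·√0.4575]² / 0.0225, which gives 163 per arm, or 182 after dividing by 0.90. For 40% against 25% the result is 152 (169), and for 50% against 35% it is 170 (189). At 180 per arm, power is 0.86, 0.84 and 0.82 for risks of 40%, 45% and 50%. The stated 15% reproduces, and the present point does not alter it.

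**2. The two texts side by side.**

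| Criterion (with parasitaemia unless noted) | Appendix 7 | Outcome form | Agree? |
|---|---|---|---|
| Early: danger signs or severe malaria | Days 1–3 | Days 0–3 | No, on Day 0 |
| Early: severe adverse event changing treatment (no parasitaemia condition) | Days 0–2 | Days 0–2 | Yes |
| Late: severe malaria | LCF | Named | Yes |
| Late: danger sign only | LCF | Not named | No |
| Late: fever or reported fever | Days 4–28 | Days 4–28 | Yes |

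The Appendix 4 flowchart, as far as its order can be read, sides with Appendix 7 in the late window: severe disease or danger signs with a positive smear leads to LCF.

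**3. Who is affected early.** Danger signs are an entry exclusion (section 5.3), so a Day 0 event in a study child begins after enrolment. Events that are severe and change treatment are ETF on both pages through "Severe AE requiring change in treatment Days 0 - 2". Repeated vomiting of study drug on Day 0 is dealt with in sections 5.3 and 6.5. What remains is a danger sign graded below severe.

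Confusion is an example. Appendix 8 lists it as a danger sign, and Appendix 9 Table A grades moderate confusion as Grade 2. With parasitaemia after dosing on Day 0, the form makes the child an ETF. Appendix 7 has no failure criterion that the child meets that day, and no exclusion in section 7.3 clearly fits.

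**4. Who is affected late.** The child must have parasitaemia and a danger sign, meet no severe-malaria criterion, have no temperature above 37.5 °C and have no reported fever in the previous 24 hours. Appendix 7 makes this LCF. On the form the LCF box can be ticked, but no listed reason matches.

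**5. Scale of one recoded child, per arm at one site.**
- Failure to non-failure: 1/180 = 0.56 points.
- Failure to no outcome, where the child also leaves the denominator: (1−p)/179. At p = 45% this is 81/180 = 45.0% against 80/179 = 44.7%, or 0.31 points. At 40% it is 0.34 and at 50% it is 0.28.
- If 1 to 4 children per arm were affected (an assumption; the documents give no rate), the first case gives 0.6 to 2.2 points (4/180 = 2.2).

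**The case against.** The strongest reply is that little of the primary outcome is exposed. A reader might infer that a convulsion after the first dose on Day 0 is a failure on the form and nothing under Appendix 7. That does not follow. Appendix 9 grades a seizure as Grade 3, section 7.2 refers any child with danger signs for parenteral quinine, and Appendix 7 therefore makes it ETF through the severe-adverse-event criterion. Several other danger signs have Grade 3 or 4 counterparts in Appendix 9 and follow the same route.

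A reader might also infer that the late case cannot be classified on the form. That does not follow either. The ETF, LCF, LPF and ACPR boxes are separate from the reasons, the key describes LCF by timing alone, and section 4.2.1 builds the endpoint from the categories and not from the reason labels. Outcome assessors are blinded (section 6.5) and the randomisation lists are per site (section 4.3), so no route to bias between the arms is shown.

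All of this stands and sets the size of the point. It does not remove the mismatch. The severe-adverse-event route depends on severity grade, and a danger sign need not be severe. The form itself lists danger signs and severe adverse events as separate reasons. The definitions to which the form defers lie outside the protocol, so they cannot be relied on to settle the conflict.

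**Conclusion.** The point holds as a contradiction in how the primary endpoint is recorded, with a probably small effect. Two things are established by the text alone: the danger-sign ETF criterion starts on Day 0 on the form and Day 1 in Appendix 7, and the form's late reason leaves out the danger signs that Appendix 7 counts. The result is possible inconsistent coding of the two narrow groups described above.

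The documents support neither a general loss of outcomes nor a count of affected children. The scale of at most 0.56 points per recoded child assumes 180 evaluable per arm at a site, and any total rests on an assumed number of such children. The sample size and the detectable difference are unaffected. The point is still worth correcting before enrolment, because this form supplies the primary outcome data.

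**What to change.** 1. Reconcile the early start day so that Appendix 7, the form's reason line and the form's key read the same. Whether that is Day 0 or Day 1 is for the investigators, because section 7.2 ties failure class to rescue treatment and the end of formal follow-up. Whichever is used, state what outcome a randomised, dosed child receives if a danger sign appears later on Day 0.
2. Name danger signs alongside severe malaria in the form's Days 4–28 reason, so that it agrees with Appendix 7.
3. Name one governing definition. Correct the reference in section 4.2.1 from Appendix 3, and have the form cite the same source, with the poster, field manual and SOP checked against it.

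The cost is a few lines in Appendix 7, the form and section 4.2.1. No analysis method or sample size changes.

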# 1.0 STUDY SUMMARY

| **Title** | **Comparison of amodiaquine + artesunate and artemether + lumefantrine for treatment of uncomplicated malaria in Uganda: evaluation of efficacy, safety, and tolerability** |
| --- | --- |
| **Description** | Randomised, single-blinded trial |
| **Participants and sample size** | Ugandans aged > 6 months recruited from 4 study sites  Total sample size 1600 subjects, 400 per site  (2 treatment arms at each site with 200 subjects per treatment arm) |
| **Clinical Sites** | The study will be conducted at 4 of Uganda Malaria Surveillance Project (UMSP) sentinel sites namely, Tororo, Kanungu, Mubende and Arua. |
| **Selection Criteria** | 1. Not previously enrolled in this study 2. Age **1 – 10 years** 3. Weight > 10 kg 4. Fever (> 37.5ºC axillary) or history of fever in the previous 24 hours 5. Absence of any history of serious side effects to study medications 6. No evidence of a concomitant febrile illness 7. Provision of informed consent and agreement to follow-up for 28 days 8. No evidence of severe malaria or danger signs 9. Absence of repeated vomiting of study medications on day 0 10. *P. falciparum* mono-infection 11. Parasite density > 2000/ul and < 200,000/ul |
| **Study intervention** | Subjects will be randomized to treatment with amodiaquine + artesunate (AQ+AS) or artemether + lumefantrine (coartemether). Subjects in the AQ+AS arm will also receive placebo tablets to ensure that the number of doses received is identical in the two treatment groups. Subjects requiring repeat therapy (second-line therapy given for symptomatic malaria) will receive quinine. |
| **Follow-up** | Subjects will be followed for 28 days and will be asked to return for follow-up assessment on days 1, 2, 3, 7, 14, 21, 28, and any unscheduled day that they feel ill. |
| **Primary outcome** | Risk of clinical rescue therapy (second-line therapy given for symptomatic malaria) |

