| **Secondary outcomes** | 1. Risk of clinical treatment failure (due to recrudescence) 2. Risk of parasitological rescue therapy 3. Risk of parasitological treatment failure 4. Risk of fever on days 1-3 5. Risk of parasitemia on days 2 and 3 6. Change in mean haemoglobin between days 0 and 28, or day of treatment failure 7. Proportion of patients with gametocytaemia during follow-up 8. Risk of serious adverse events during follow-up 9. Risk of adverse events of moderate or greater severity, at least possibly related to the study medications, excluding patients requiring rescue therapy |

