### 4.2.3 Secondary outcomes

1. Risk of clinical treatment failure
2. Risk of parasitological rescue therapy
3. Risk parasitological treatment failure
4. Risk of fever during the first 3 days of follow-up: presence or absence of objective fever (axillary temperature > 37.5C) or patient report of fever on days 1, 2, 3
5. Risk of parasitemia on follow-up days 2 and 3: proportion of positive vs. negative thick blood smears on day 2 and day 3
6. Change in mean haemoglobin from day 0 to 28 or day of repeat therapy
7. Proportion of subjects lacking gametocytes on day 0 with gametocytaemia on any follow-up day
8. Risk of serious adverse events: proportion of patients experiencing any serious adverse event in each treatment group during the 28-day follow-up period, excluding treatment failures
9. Risk of adverse events of moderate or greater severity, at least possibly related to the study medications, excluding treatment failures.

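### Early treatment-limiting adverse events are coded as treatment failures, and the safety outcomes exclude treatment failures under wordings that differ between sections

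*Protocol*

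**What the plan says.** **Failure coding.** Appendix 7 lists five ETF criteria. Four require parasitaemia. The fifth, "Severe AE requiring change in treatment Days 0 - 2", does not. The outcome form in Appendix 12 repeats it as a reason for clinical failure ("Severe AE requiring change in treatment Days 0-2"), so the rule is operational. Section 4.2.1 states "All ETFs will be considered true treatment failures", defines the primary outcome by "Clinical rescue therapy = ETF + LCF", and puts all ETFs into both genotype-adjusted failure outcomes. The study summary (section 1.0) describes the primary outcome as "Risk of clinical rescue therapy (second-line therapy given for symptomatic malaria"), which a drug reaction without malaria symptoms does not fit.

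**Safety outcomes.** The exclusions in the two sections do not match:

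| Outcome | Section 1.0 | Section 4.2.3 |
| --- | --- | --- |
| 8, serious AEs | no exclusion | "proportion of patients experiencing any serious adverse event in each treatment group during the 28-day follow-up period, excluding treatment failures" |
| 9, moderate or greater, at least possibly related AEs | "at least possibly related to the study medications, excluding patients requiring rescue therapy" | treatment failures excluded |

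Neither section says whether treatment failure here means failure before or after genotyping.

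**The concern.** Safety and tolerability are in the title and the study aim. Section 2.1.1 says that concern about the safety and tolerability of amodiaquine may limit support for AQ+AS, and section 2.3 says that the results go directly to the Ministry of Health. Under these definitions, a reaction bad enough to force a change of treatment on Days 0-2 is added to the failure count. It is then removed from the safety comparison meant to show it.

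A second problem follows from the same wording. Leaving out patients because they were rescued is a selection made after randomisation and on the basis of outcome. If efficacy differs between the arms, the share removed differs too, and the remaining groups are no longer the randomised ones.

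**Working it through.** **1. The plan's own figure.** Section 9.1 gives 200 patients per arm per site, 10% loss, two-sided α = 0.05, 80% power, an AQ+AS rescue risk of 40-50% and a detectable difference of about 15 points. With 200 × 0.9 = 180 evaluable per arm and the pooled-variance formula n = [1.96·√(2p̄(1−p̄)) + 0.842·√(p₁(1−p₁) + p₂(1−p₂))]² / (p₁−p₂)², the detectable decrease is 13.9, 14.3 and 14.6 points at control risks of 40%, 45% and 50%. With continuity correction it is 14.4, 14.9 and 15.2. The stated figure reproduces. It does not decide this point and only supplies inputs for step 3.

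**2. Tracing one patient.** Take a child with a severe, possibly drug-related reaction on Day 1 whose treatment is changed.
- Appendix 7: ETF. Section 4.2.1: true treatment failure, and a clinical rescue therapy event, because that category is ETF plus late clinical failure.
- Outcome 9, section 4.2.3: out, as a treatment failure. Outcome 9, section 1.0: out, as a rescued patient on the section 4.2.1 definition.
- Outcome 8: relevant only if the event meets the seriousness criteria of section 8.1, since severe is a grade and serious is not. If it does, the child is out under section 4.2.3 and in under section 1.0.
- If the exclusion is read as dropping events rather than patients, the AE is itself the event that defines the failure, so it is still dropped.

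**3. Share of outcome 9 lost if rescued patients are excluded.** Four sites × 200 = 800 per arm.
- AQ+AS: 0.40 × 800 = 320 to 0.50 × 800 = 400 removed, leaving 480 to 400.
- Coartemether, only if its risk were 15 points lower: 0.25 × 800 = 200 to 0.35 × 800 = 280 removed. The 15 points are the detectable difference, not a forecast, so this only illustrates the imbalance.

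**4. Precision of outcome 8 for AQ+AS.** With zero events, the approximate 95% upper limit is 3/n.

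| Meaning of the exclusion | n | 3/n |
| --- | --- | --- |
| None (section 1.0) | 800 | 0.38% |
| Genotype-adjusted clinical failures, 4-12% (AQ+AS, Table 1) | 768 to 704 | 0.39-0.43% |
| All rescued patients, 40-50% | 480 to 400 | 0.63-0.75% |

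Here 800 × 0.96 = 768 and 800 × 0.88 = 704. Table 1 covers children under 5 years. Of its AQ+AS sites only Tororo is in this trial, and it supplies the 12%. Its rescue risk there is 55%, so the two readings differ widely.

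**5. Number of AE-defined ETFs.** The protocol gives no rate. At an assumed 0.5% to 3%, 0.005 × 800 = 4 to 0.03 × 800 = 24 patients per arm would be added to the failures (0.5 to 3 points), and none would remain in outcome 9.

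**The case against.** **The exclusion has a plausible purpose.** Appendix 9, Table A grades any reported fever in the past 24 hours as moderate, and recurrent malaria also brings weakness, anorexia and vomiting. Counting these as AEs would charge each arm for its recurrences. This stands, and the fix must handle it. It does not justify removing whole patients or drug reactions.

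**Counting treatment-limiting toxicity as failure is a deliberate composite.** This also stands. Taking these patients out of failure and censoring them at the switch is not clearly better, because such censoring may be informative.

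**The events may be rare.** Section 12.2.6 reports 20 severe AEs in 1869 coartemether patients (20/1869 = 1.1%). Of these, 19 were likely due to malaria or other illness, and one was possibly related but occurred 13 days after the last dose. Section 12.2.4 cites no severe or life-threatening event in a review of 40 amodiaquine trials. Section 12.2.5 cites no serious event in 9,241 artemisinin patients. These sources may not capture every tolerability-driven switch, but they argue against assuming a large number.

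**Nothing is lost from the data.** AEs of moderate or greater severity are recorded (section 8.3), and the outcome form names the severe AE as the failure reason. True: the loss is from the defined between-arm outcomes. An analysis plan could add a safety set, but the protocol has already fixed exclusions, and they conflict.

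**Stronger readings that do not hold.** A reader might infer that the worst toxicity vanishes from both safety outcomes. The documents do not support that: the rule covers only Days 0-2, severe does not mean serious, and section 1.0 has no exclusion for outcome 8. A reader might also take 0.63-0.75% as the serious-AE limit. That applies to outcome 8 an exclusion of rescued patients that section 1.0 attaches only to outcome 9. Section 4.2.1 separates rescue therapy from treatment failure. The wide meaning remains possible, because the Table 1 footnote also speaks of treatment failure before genotyping, but it is one end of a range.

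**Conclusion.** The point holds within limits. Early treatment-limiting drug reactions drop out of outcome 9 under either section, taking rescue therapy as section 4.2.1 defines it. They drop out of outcome 8 only when the event is serious and section 4.2.3 governs. Their number is unknown and may be small.

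The larger quantifiable effect is on outcome 9. Excluding rescued patients would remove about 40-50% of the AQ+AS arm on the protocol's own risk estimate, with a different share in the other arm if efficacy differs. For outcome 8 the loss of precision runs from negligible (0.38% to 0.39-0.43%) to a near doubling (0.63-0.75%), depending on a meaning that the protocol leaves open. The definitions should be settled before analysis, since safety is a named aim and the correction needs no new data.

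**What to change.** 1. Reconcile sections 1.0 and 4.2.3 under one wording. Analyse outcomes 8 and 9 in every randomised patient who took at least one dose, counting events up to rescue therapy or Day 28.
2. Delete the patient-level exclusions. Omit only the malaria recurrence and the symptoms attributed to it on the day of failure.
3. State that the AE that defines an ETF always counts in outcome 9, subject to that outcome's relatedness criterion, and in outcome 8 if it is serious.
4. Keep the ETF composite, but show AE-defined ETFs as a separate line in the efficacy tables. Add a sensitivity analysis of the failure outcomes that does not count them as failures.

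The cost is wording in sections 1.0 and 4.2.3, one table line and one sensitivity analysis. The outcome form already identifies these patients, and no rule of patient care changes. The downside is that AE rates may look slightly less favourable, and some malaria symptoms may need a relatedness judgement, best made by the blinded clinicians.
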